#### Intervention description {11a}

GBH granules are produced and packaged by Hanpoong Pharm & Food Co., Ltd., (Jeonju, Korea) under good manufacturing practices (GMPs). GBH extract consists of *Cinnamomi Ramulus*, *Poria Sclerotium*, *Moutan Radicis Cortex*, *Persicae Semen*, and *Paeoniae Radix* (Table 1). A gramme of GBH granule contains 443.33 mg of GBH extract, lactose hydrate, and corn starch. Participants in the high-dose group will be administered three GBH granule sachets (1.5 g each, total 4.5 g) twice a day, for 8 weeks. Participants in the low-dose group will be treated with one GBH granule (1.5 g each, total 1.5 g) and two placebo granule sachets (1.5 g each, total 3 g) orally twice a day, for 8 weeks (Table 2). The high-dose GBH (GBH extract 3,900mg/day) is identical to the approved dose of GBH for another indication. Meanwhile, the low-dose GBH (GBH extract 1300mg/day) was calculated based on the human equivalent dose [20] converted from the optimal dose identified in a mouse model of depression.

**Table 1 Tab1:** Ingredients and composition of GBH extract

Herbal name	Source species	Parts used	Composition ratio
Cinnamomi Ramulus	*Cinnamomum cassia* J. Presl	Branch	1
Poria Sclerotium	*Poria cocos* Wolf	Sclerotium	1
Moutan Radicis Cortex	*Paeonia suffruticosa* Andrews	Rhizodermis	1
Persicae Semen	*Prunus persica* Batsch	Seed	1
Paeoniae Radix	*Paeonia lactiflora* Pallas	Root	1

**Table 2 Tab2:** Doses of GBH granules in three groups

Group	Daily dose	Daily dose of active ingredient
High-dose GBH	GBH granule 9 g	GBH extract 3900 mg
Low-dose GBH	GBH granule 3 g + placebo granule 6 g	GBH extract 1300 mg
Placebo	Placebo granule 9 g	None

#### Criteria for discontinuing or modifying allocated interventions {11b}

Participants are considered for treatment cessation and elimination from the study if they meet the following criteria.Participants who do not meet inclusion and exclusion criteriaParticipants with serious adverse events (SAEs)Participants with adverse events warranting discontinuation of study drugParticipants with symptom aggravation and in need of another treatmentParticipants who withdraw consentParticipants who are lost to follow-upParticipants whose compliance with treatment is below 70%Participants who are unsuitable for continuing administration by the investigators

Additionally, procedures for assessing suicide risk of participants and discontinuing intervention in case of high suicide risk were established. During 8 weeks of treatment, the depressive symptoms of participants including suicide risk will be assessed every 2 weeks. Assessment of suicide risk will be carried out using the third item of HDRS and semi-structured interview for assessing suicide risk. High suicide risk will be determined by the researcher based on the presence of specific suicide ideation or suicide attempt. Participants with high suicide risk will be discontinued from the study immediately and transferred for appropriate management and treatment.

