### Data collection and management

#### Plans for assessment and collection of outcomes {18a}

##### Primary outcome

HDRS is a representative clinician rating scale for depression. It consists of 17 items measuring the severity of depressive symptoms, and the HDRS-17 total scores range from 0 to 52, with the higher score indicating severe symptoms [28, 29]. The Korean version of HDRS validated in 2005 will be used in this study [30]. HDRS will be evaluated by trained investigators working as fellows or residents at the Department of Neuropsychiatry in Korean medicine. To ensure the consistency of HDRS, the investigators from three sites met to conduct training and discussion sessions before the initiation of clinical trial. The HDRS assessment will be carried out according to the Structured Interview Guide for the Hamilton Depression Rating Scale (SIGH-D) [31]. HDRS will be measured every 2 weeks during the 8 weeks of administration (week 0, 2, 4, 6, 8) and follow-up assessment (week 12).

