#### Methods for additional analyses (e.g., subgroup analyses) {20b}

##### Additional analyses using repeated measures

The Linear Mixed Model (LMM) will be used to analyse the effect of group on continuous variables (HDRS-17 total score, HDRS-6 subscale, BDI-II, ISI, STAXI, and EQ-5D index) over time. Also, the generalised estimating equations (GEE) analysis will be used to analyse the effect of group on binary variables (HDRS response and remission) over time.

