#### Methods in analysis to handle protocol non-adherence and any statistical methods to handle missing data {20c}

##### Definition of analysis population

Full analysis set will include all randomised participants, except as follows:Participants who are found to be ineligible for the trial after randomisationParticipants who have never been exposed to the investigational productParticipants who have never been assessed after randomisation

Per protocol set will include participants who have completed the trial process without violating the protocol. The following participants will be excluded from the per protocol set.Participants who dropped out from the trialParticipants who are found to be ineligible for the trialParticipants with less than 75% compliance with the study treatment protocolParticipants who are considered as a major violation for any other reason

Safety set will include all participants who have received the intervention at least once. Participants who have never been treated with the investigational product will be excluded from the safety set.

For the efficacy outcome analysis, the full analysis set will be mainly analysed, and per protocol set will be additionally analysed. A safety set will be used for the safety analysis. Multiple imputations will be performed to handle missing data.

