## Discussion

This randomised controlled trial is designed to investigate the safety and efficacy of GBH compared with placebo, in patients with major depressive disorders. Also, this trial is designed to determine the optimal dose of GBH for major depressive disorders, for further investigation in a phase III trial.

GBH granule is one of the products of herbal medicine manufactured by various pharmaceutical companies according to the Korean Herbal Pharmacopoeia (KHP) and following good manufacturing practice (GMP) guidelines. GBH is approved by the Korean MFDS for the following indications: dysmenorrhea, menstrual cramps, menopausal disorders, dizziness, and bruise. In case of approved herbal medicines with the target indication out of range for the indications previously specified, an investigational new drug (IND) application for a new indication is required in Korea [46]. Depressive disorder was not one of the previously approved indications for GBH. This trial protocol was approved by Korean MFDS in October 2018, and the trial was initiated in December 2019.

Various clinical trials have been conducted to explore the efficacy of herbal medicines for depression [47–49]. Previous randomised trials mostly included patients with mild-to-moderate depression [47]. In this trial, we plan to enrol patients with moderate depression whose HDRS-17 total score is 18 or higher. Also, patients who are undergoing treatment with antidepressants will be excluded from the trial, and the efficacy and safety of GBH monotherapy compared to placebo will be examined. Intensive and close monitoring of suicide risk factors will be conducted to prevent and minimise the risk.

The novel herbal composition of GBH is designed for patients with depression. In previous randomised trials of depression, *Bupleuri Radix*, *Angelicae Sinensis Radix*, *Paeoniae Radix*, and *Poria Sclerotium* were frequently used [47]. GBH also contains *Poria Sclerotium* and *Paeoniae Radix*. The other herbal components of GBH include *Cinnamomi Ramulus*, *Moutan Radicis Cortex*, and *Persicae Semen*. The composition of GBH also differs from the frequently used prescription pattern recommended for depressive disorders in Taiwan [50]. Based on the results of in vivo studies of GBH, amelioration of depression is expected.

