## Trial status

Recruiting for the trial started in December 2019. The current protocol represents version 2.8 of 28-5-2020. Patient recruitment is estimated to be completed around May 2022.

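### One list governs both stopping study drug and leaving the study, so the week-8 HDRS-17 can be lost for reasons that may depend on treatment.

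*Protocol article*

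**What the plan says.** In the protocol article, the section on criteria for discontinuing or modifying allocated interventions {11b} introduces its list with "Participants are considered for treatment cessation and elimination from the study if they meet the following criteria". The same list therefore serves for ending treatment and for ending participation. It holds eight criteria: ineligibility, serious adverse events, adverse events that justify stopping drug, worsening that calls for other treatment, withdrawn consent, loss to follow-up, compliance below 70%, and unsuitability in the investigator's view.

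On suicide risk the section first says that "procedures for assessing suicide risk of participants and discontinuing intervention in case of high suicide risk were established", and then that "Participants with high suicide risk will be discontinued from the study immediately and transferred for appropriate management and treatment". The first sentence is about drug, the second about the study.

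Other sections bear on the point:

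- Outcomes {12}: the primary outcome is the change in HDRS-17 from baseline to week 8.
- Plans for assessment {18a}: "HDRS will be measured every 2 weeks during the 8 weeks of administration".
- Definition of analysis population {20c}: the full analysis set is the main efficacy set. It leaves out people found ineligible, never exposed, or never assessed after randomisation. The per protocol set leaves out drop-outs and anyone below 75% compliance. On gaps: "Multiple imputations will be performed to handle missing data".
- Additional analyses {20b}: "The Linear Mixed Model (LMM) will be used to analyse the effect of group on continuous variables", over time.
- Retention {18b} covers visit scheduling, reminders and questionnaire checks. Post-trial care {30} covers a week-12 observation after completed treatment and care for adverse events. Neither mentions an HDRS rating after an early stop.

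**The concern.** Stopping drug and leaving the study are different events. Stopping drug is a clinical decision; the participant can still be rated. Leaving the study ends the data. When one list triggers both, someone who stops drug because of side effects can also lose the primary outcome.

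Several listed reasons arise after randomisation and may depend on the arm or on the course of depression. If they remove more people from one arm, or different kinds of people, the observed week-8 scores come increasingly from those who tolerate and take the drug. The Objectives {7} use the effect sizes to judge whether a phase III trial is feasible, and the Discussion uses the trial to choose a dose. A difference in tolerability between the two doses could therefore disturb the dose comparison as well as each comparison with placebo.

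**Working it through.** **1. Which criteria can cost a week-8 score?**

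- *Adverse events, serious or not.* They can occur at any time and plausibly depend on dose. This is the clearest route.
- *Compliance below 70%.* The protocol does not say when or over what period this is calculated. Returned drug is counted at the two-weekly visits (adherence section {11c}). If the rule is applied at those visits, removal can come before week 8. If it is applied to the whole 8 weeks, it is settled at about the week-8 visit and costs little.
- *Worsening that needs other treatment, and high suicide risk.* These are tied to the outcome, but a later score may reflect the other treatment, or rating may not be feasible after transfer.

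**2. Is removal for low compliance needed?** Anyone below 70% is also below 75%, and so is already outside the per protocol set. Removal adds nothing to that analysis and can only take data from the full analysis set.

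**3. Who leaves the full analysis set?** Only those with no assessment after randomisation. Compliance and suicide risk are checked at the two-weekly visits, when HDRS is also rated, so people removed on those checks would normally have at least one score. Loss from the set is realistic mainly for stops before week 2, such as early adverse events. The others stay in and are imputed.

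**4. The plan's own figures.** Sample size {14} gives a difference of 4, SD 5.78, two-sided 5% and 80% power. A two-sample t-test with the noncentral t distribution gives 33.765 per group, matching the stated 33.77. Then 33.77/0.8 = 42.2, stated as 42. The 20% allowance is 0.20 × 42 = 8.4 per group, or 0.20 × 126 = 25.2 in all. It protects power, not against bias.

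**5. Illustration of bias.** Let p be the share removed and d the amount by which the true week-8 score is worse than the imputed one, in the active (A) or placebo (P) arm. The benefit is overstated by

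bias = pA × dA − pP × dP.

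The document gives no value for p or d; all of these are assumptions.

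| Assumption | Bias (points) |
|---|---|
| Both arms 10%, d = 4 | 0.10 × 4 − 0.10 × 4 = 0 |
| Active only, 5%, d = 2 | 0.05 × 2 = 0.1 |
| Active only, 5%, d = 4 | 0.05 × 4 = 0.2 |
| Active only, 10%, d = 4 | 0.10 × 4 = 0.4 |
| Placebo only, 10%, d = 4 | −0.10 × 4 = −0.4 |
| Active only, 20%, d = 4 | 0.20 × 4 = 0.8 |
| Active only, 20%, d = 6 | 0.20 × 6 = 1.2 |

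For scale, 0.4 is 0.4/4 = 10% of the target difference. The unadjusted standard error of a difference is 5.78 × √(2/42) = 1.26 with 42 per arm and 5.78 × √(2/34) = 1.40 with 34, so 0.4 is 0.32 or 0.29 standard errors.

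**The case against.** The best reply is that loss of the week-8 score is inferred. The list says participants are considered for removal, which leaves discretion. No section says a rating would be refused, and the unseen full protocol may provide an early-termination visit. The main analysis keeps drop-outs who have an assessment and imputes them, and the mixed model uses the two-weekly scores. For people who start other treatment, setting later scores aside may suit the stated aim that "the efficacy and safety of GBH monotherapy compared to placebo will be examined". And this is an exploratory phase II trial.

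Much of this stands. A reader might infer that everyone who meets a criterion loses the primary outcome or falls out of the full analysis set; the documents support neither. A reader might also treat low compliance as certain to cost scores; that depends on when the 70% rule is applied.

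What does not fall away is the rule itself. The article is not merely silent on follow-up after stopping drug: it states elimination, and no section shown offsets that. Imputation from scores before the stop helps, but it rests on an assumption about the course afterwards that those scores cannot test.

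**Conclusion.** The point holds as a design weakness worth a cheap correction. The rule can lose week-8 HDRS-17 values for reasons that may depend on treatment, most clearly adverse events. Removal for low compliance brings no gain to the analysis.

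The size and direction of any bias cannot be found from the document. It may be zero, and it may favour either arm. The range of 0-0.4 points is an illustration that assumes removal in the active arm only, 5-10% removed, and true scores 0-4 points worse than imputed. A reader might take 0.4 or 0.8 as an upper limit, but neither is one: someone who deteriorates after stopping could differ from the imputed score by more than 4 points, and the 20% drop-out is a planning rate, not a maximum. Nor do the documents support a claim that the bias flatters GBH.

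**What to change.** Amend the discontinuation section as follows:

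1. Make every criterion except withdrawn consent and loss to follow-up a reason to stop study drug only. Keep immediate transfer for high suicide risk.
2. Delete compliance below 70% as a reason to leave the study.
3. Seek the already scheduled week-8 HDRS-17 from those who stop drug, unless consent for follow-up is withdrawn or rating is clinically inappropriate.
4. Include observed week-8 scores of those who stop for adverse events or low compliance in the full analysis set, as randomised.
5. For those who start other depression treatment, record it and state in advance whether the main analysis uses their observed scores or sets them aside and imputes. Report the alternative as a sensitivity analysis.

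The cost is an amendment and already scheduled visits for those who stop drug: about 25 participants at the planned 20% drop-out, fewer if some have withdrawn consent or been lost. It helps only participants not yet past week 8. Recruitment began in December 2019, and the Trial status section says "Patient recruitment is estimated to be completed around May 2022". The downside is that some scores will be affected by other treatment, possibly unequally by arm, and that rating may not be possible for people transferred elsewhere.

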#### Strategies to improve adherence to interventions {11c}

To evaluate treatment adherence, the amount of drug return will be checked at every visit when participants visit the hospitals every 2 weeks during 8 weeks of administration. The investigator and clinical research pharmacist will determine the compliance of each participant and instruct them not to overdose.

#### Relevant concomitant care permitted or prohibited during the trial {11d}

##### Concomitant medication and care prohibited during the trial

Anxiolytics, antidepressants, antipsychotics, corticosteroids, female hormones, thrombolytic, blood coagulation inhibitor, L-dopa, Digitalis, bromide, cyclosporin, disulfiram, isoniazid, and yohimbineMedications for treating or improving the symptoms of major depressive disordersMedications that may affect the degree of depressionOther herbal medicines or dietary supplementsNon-pharmacologic interventions for improving depressive symptoms (e.g., acupuncture, relaxation therapy, electroconvulsive therapy (ECT), vagal nerve stimulation (VNS), deep brain stimulation (DBS), light therapy, or transcranial magnetic stimulation (TMS))

##### Concomitant medication permitted during the trial

Concomitant medications will be permitted based on the judgement of investigators, if the drugs are not prohibited during the trial and administered for more than 4 weeks during the screening period.

#### Provisions for post-trial care {30}

Follow-up observation will be performed at week 12, 4 weeks after the completion of the 8-week treatment. In case of adverse events, the investigator will evaluate the follow-up observations and provide the requisite treatment until the symptoms disappear.

#### Outcomes {12}

##### Primary outcome

The primary outcome is the change from the baseline HDRS-17 total score at week 8 (post-treatment). Baseline HDRS-17 total score and site will be used as the covariate. The change from the baseline in HDRS-17 total score at week 8 will be compared in groups treated with low-dose GBH and placebo, and high-dose GBH and placebo.

##### Secondary outcomes

Change from the baseline HDRS-6 subscale at week 8 (post-treatment)HDRS response: proportion of participants with HDRS-17 total score reduced below 50% of the baseline score at week 8 (post-treatment)HDRS remission: proportion of participants, whose HDRS-17 total score is less than 7 [21] at week 8 (post-treatment)Change from the baseline BDI-II score at week 8 (post-treatment)Change from the baseline Insomnia Severity Index (ISI) score at week 8 (post-treatment)Change from the baseline anxiety state and anxiety trait in the State-Trait Anxiety Inventory YZ form (STAI-YZ) score at week 8 (post-treatment)Change from the baseline anger state, anger trait, anger in, anger out, and anger control of State-Trait Anger Expression Inventory (STAXI) score at week 8 (post-treatment)Change from the baseline 3-level version of EQ-5D (EQ-5D-3L) index at week 8 (post-treatment)

##### Exploratory outcomes

Korean Symptom checklist-95 (KSCL95) [22] will be measured at weeks 0, 4, 8, and 12. *T* scores of depression, anxiety, phobic anxiety, obsessive-compulsive disorder, post-traumatic stress disorder, aggressive state, somatisation, manic, paranoid ideation, schizophrenia, suicide, addiction, sleeping problems, and stress vulnerability will be calculated.Pattern identification tool for depression (PIT-D) [23, 24] will be used at weeks 0, 4, 8, and 12. Pattern scores of stagnation of liver qi, deficiency of the heart and spleen, yin deficiency with excessive fire, qi deficiency with phlegm, and stagnation of qi with fire will be calculated.Saliva melatonin and cortisol at 10 am will be measured at weeks 0, and 8.

### Participant timeline {13}

[figure not shown]

### Sample size {14}

Sample size was computed to detect the mean difference in change from the baseline HDRS-17 total score between placebo and low-dose GBH groups. The mean difference in scores between the two groups was assumed as four, which was reported to be the threshold points for minimal improvement in patients’ perspectives [25, 26]. Also, standard deviation was estimated to be 5.78, based on the results of a similar clinical trial of *Danzhiningshen* involving patients with depression [27]. The herbal composition of GBH and Danzhiningshen differs, but the two formulae contain *Moutan Radicis Cortex*. With a two-sided significance level of 5% and a power of 80%, 33.77 participants are required in each group of the trial. Considering the drop-out rate of 20%, 42 participants will be recruited per group, and a total of 126 will be investigated.

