### Trial design {8}

This study will be a randomised, double-blind, placebo-controlled, and multi-arm parallel-group trial. Participants will be allocated in a 1:1:1 ratio to one of three parallel groups: high-dose GBH, low-dose GBH, and placebo. The HDRS-17 total scores in high-dose and low-dose GBH groups will be compared with those of the placebo group.

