### Statistical methods

#### Statistical methods for primary and secondary outcomes {20a}

##### Primary outcome

The change from the baseline in HDRS-17 total score at week 8 (post-treatment) among the three groups will be compared via analysis of covariance (ANCOVA). The group will be used as the fixed factor, and baseline HDRS-17 total score and site will be used as the covariate. The effect of group on HDRS-17 total score after adjusting for baseline score and site will be calculated. Subsequent pairwise comparisons will be performed with low-dose GBH vs placebo and high-dose GBH vs placebo using Dunnett’s test. The least square mean and standard error of three groups, and the estimated mean difference (95% CI) and adjusted *p*-value compared with placebo group will be presented.

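### The stated 80% power belongs to one unadjusted t-test of low dose against placebo; under the planned Dunnett test it is about 72-73% at the evaluable number the protocol assumes

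*Protocol article*

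**What the plan says.** Protocol article, Sample size {14}, names the comparison that was sized: "Sample size was computed to detect the mean difference in change from the baseline HDRS-17 total score between placebo and low-dose GBH groups". Its inputs are an effect, "The mean difference in scores between the two groups was assumed as four", and a spread, "standard deviation was estimated to be 5.78". The result is "With a two-sided significance level of 5% and a power of 80%, 33.77 participants are required in each group of the trial". The allowance for losses follows: "Considering the drop-out rate of 20%, 42 participants will be recruited per group, and a total of 126 will be investigated". The section mentions no multiplicity adjustment.

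The primary analysis is in Statistical methods for primary and secondary outcomes {20a}, Primary outcome. It is a three-group ANCOVA with baseline HDRS-17 and site as covariates, and then: "Subsequent pairwise comparisons will be performed with low-dose GBH vs placebo and high-dose GBH vs placebo using" Dunnett's test, with adjusted p-values to be reported. Trial design {8} fixes equal arms: "Participants will be allocated in a 1:1:1 ratio to one of three parallel groups". Objectives {7} sets the primary aim as finding whether at least one of the two doses works.

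**The concern.** The power statement and the primary test do not belong together. A sample size worked out for one comparison at the full two-sided 5% level is smaller than the size needed when two doses share that 5% through Dunnett's test. The 80% is attached by name to low dose against placebo, so anyone who later reads a non-significant low-dose result will set it against a type II error of 20%. On the protocol's own inputs and drop-out rate, the planned test has a type II error nearer 28%. The mismatch lies between two sections of the same document, so it is not a detail left to a later analysis plan.

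**Working it through.** **Inputs.** Difference d = 4, SD s = 5.78, two-sided 5%, power 80%, drop-out 20% and 42 recruited per arm, all from Sample size {14}. Two dose-placebo comparisons with Dunnett's test, from {20a}. Equal arms from {8}, so the two contrasts have correlation 0.5.

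**Step 1: reproduce the stated figure.**
- Normal approximation: n = 2[s(1.960 + 0.842)/d]² = 32.8 per group. This is not the stated value.
- Two-sample t-test, noncentral t, df = 2n − 2, unadjusted 5%: 80% power at n = 33.765, that is, 33.77 as stated.
- With Bonferroni at 2.5%, n = 39.7 (normal approximation); with Dunnett, n = 39.8. Neither lies behind 33.77.

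**Step 2: evaluable number.** 42 × 0.8 = 33.6 per arm. The stated requirement rounded up is 34.

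**Step 3: power per dose, unadjusted and under Dunnett.** The noncentrality is d/(s√(2/n)). At n = 33.6 it is 4/(5.78 × 0.2440) = 2.837; at 34 it is 2.853; at 42 it is 3.171. For Dunnett, df = 3n − 6 (three groups, baseline, three sites).

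| n per arm | Unadjusted t-test (critical value about 2.00 at n = 33.6 and 34) | Dunnett critical value | Dunnett power per dose |
|---|---|---|---|
| 33.6 | 79.8% | 2.245 | 72.2% |
| 34 | 80.3% | 2.245 | 72.8% |
| 42 (all complete) | 88.0% | 2.238 | 82.3% |

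For 80% per dose under Dunnett, 39.8, so 40, evaluable per arm are needed: 40/0.8 = 50 recruited per arm and 150 in all, against 126.

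**Step 4: covariate adjustment (an assumption; the document gives no correlation).** If the covariates correlate r with the endpoint, s becomes s√(1 − r²). Dunnett power at 34 per arm is 75%, 77%, 81% and 85% for r = 0.2, 0.3, 0.4 and 0.5. The value that restores 80% is r = 0.385.

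**Step 5: at least one dose significant, 34 per arm, by simulation without covariate gain.**

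| True differences, two doses | Power for at least one |
|---|---|
| 4 and 4 | 86% |
| 4 and 2 | 74% |
| 4 and 0 | 74% |

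If both doses truly give 4 points, the chance that both reach significance is about 59%.

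**The case against.** The strongest reply is that 72-73% is a floor. It supposes that patients who drop out contribute nothing and that the covariates explain nothing. The article plans otherwise: HDRS is rated at weeks 2, 4 and 6 as well as week 8 ({18a}); the full analysis set keeps eligible, treated patients with any assessment after randomisation, with multiple imputation ({20c}); and the ANCOVA adjusts for baseline and site ({20a}). Modest gains from both sources would be enough. For instance, an effective 36 per arm with r = 0.3, or 38 with r = 0.2, gives about 80%; 36 with no covariate gain gives 75%. This stands as far as it goes, and it rules out saying flatly that power at the planned size is 72%, since at 42 complete per arm it is 82%. But how much would be recovered is unknown, the protocol claims no such gain, and its own calculation inflates for drop-out, which presumes that those patients are lost to the comparison.

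A second reply is that the stated aim is at least one effective dose, for which power is 74% to 86%. That is fair, and those figures belong in the text. They do not rescue the stated 80%, which is tied to the low-dose comparison.

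A reader might also infer three stronger points that the article does not support:
- **A phase III decision made on a wrong type II error.** Objectives {7} rests phase III feasibility on effect sizes, and {20a} reports mean differences with 95% confidence intervals, which show directly whether 4 points remains plausible.
- **An overall F test acting as a gate and costing further power.** The wording gives an order, not a condition, and Outcomes {12} states the pairwise comparisons without one.
- **A rounding fault in "Considering the drop-out rate of 20%, 42 participants will be recruited per group".** Indeed 33.77/0.8 = 42.2 would round up to 43, but stopping at 42 leaves 79.8% unadjusted power, about 0.2 points short.

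**Conclusion.** The concern holds in a limited form. The 80% is the power of a single unadjusted two-sided 5% t-test of low dose against placebo, not of the Dunnett comparison that the protocol will make. With a 4-point difference and SD 5.78, the like-for-like power is 72.2% to 72.8% on the protocol's own drop-out premise, a shortfall of 7 to 8 percentage points. The figure assumes no information from drop-outs and no covariate gain; with all 42 per arm complete it is about 82%, so the shortfall depends on losses and on how well the covariates predict the outcome. The weight is moderate: the trial is exploratory, Dunnett's test keeps the family-wise type I error at 5%, and no estimate or test is affected.

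**What to change.** Keep 126 patients and the Dunnett analysis. Reword Sample size {14} to say that:
- 33.77 per group gives 80% power for an unadjusted two-sided 5% t-test of low-dose GBH against placebo;
- under the planned Dunnett test, power per dose at a 4-point difference and SD 5.78 is about 72-73% with about 34 evaluable per arm, and about 82% if all 42 are complete, with no covariate gain assumed;
- power to show at least one dose effective, at about 34 evaluable per arm, is about 74% if only one dose gives 4 points and about 86% if both do.

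The cost is wording and a less favourable stated power. No patients are added and the design and analysis do not change. Sizing on Dunnett instead would need 50 per arm, 150 − 126 = 24 more patients, which is hard to justify in an exploratory trial already recruiting.
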